**Fig. 3 Fig3:**
[figure not shown]
SPIRIT checklist, describing the outcome measures and the time-points of evaluation

### Statistical analysis

#### Sample size

We propose a sample size based on an effect size of treatment of 130 s of difference in seconds of CWRET between the groups. The estimated improvement (mean and standard deviation) in the control group was calculated in relation to previous studies [36], defining 150 s as the minimally clinically important difference of improvement of CWRET after rehabilitation. The improvement in the treatment group was estimated by an internal pilot study conducted in 10 patients. A total of 156 participants would provide 90% power to detect 130 s (SD 250) difference between the groups, with 5% significance. Due to a high expected drop-out rate (patients transferred to acute care, severely ill with fever, severe dyspnoea, acute respiratory failure, etc.) we will enrol at least 170 patients. We expect a recruitment rate of at least 23 patients per centre.

#### Analysis plan

Details about project start-up phase and patient recruitment are reported in ClinicalTrials.gov ID NET03322787. Statistical analysis will be performed using STATA 11 (StataCorp LLC, Texas 77845–4512 USA).

Continuous variables with normal distribution will be presented as mean ± standard deviation (SD), if non-normally distributed, as median and interquartile range. The distribution of continuous variables will be verified by the Shapiro–Wilk test. Binary and categorical outcomes will be described using frequencies and percentages in each group.

The primary analysis will be a modified intention-to-treat analysis, including all randomly assigned participants for whom data on the primary endpoint is available. Secondary analysis will be conducted per-protocol (all completers).

Primary analysis of the primary outcome will be through a linear regression model considering the outcome measures at the end of the training as a dependent variable and intervention/control as an explanatory variable with adjustment for the baseline value of the primary outcome. The model will also take into account the centre as a stratification variable.

The baseline, follow-up values and the unadjusted change in outcome measures between baseline and the end of study for both groups will be also presented.

Secondary analysis will consist of a two-sample *t* test comparing differences in the changes in all outcome measures after rehabilitation between the intervention and control groups.

In order to define which baseline characteristics are related to the improvement of primary outcome and to drop-out event, we will perform an explanatory data evaluation analysing the odds ratio (with corresponding 95% confidence intervals and *P* values) of improvement/non-improvement on CWRET above 150 s [36] and the completion/dropout of the programme for each baseline variable. A *P* value of < 0.05 will be considered statistically significant.

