### Randomisation

The participants will be randomised in variable blocks by centres. Enrolled patients will be randomised to either an intervention or a control group (randomisation ratio 1:1). The allocator will be a researcher not involved in the study, blinded on group allocation. The allocator will generate a randomisation list by a dedicated software (https://www.randomizer.org/). When a new patient (after control of eligibility and signing of informed consent) will need to be enrolled, care providers from each centre will contact the randomisation centre by phone for definitive allocation. Patients will be aware of their allocation.

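### The primary analysis drops every patient without an end-of-training CWRET although loss through deterioration is expected, and the only other stated analysis set cannot reveal any resulting bias

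*Protocol article*

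**What the plan says.** The Analysis plan section of the protocol article calls the primary analysis modified intention-to-treat, "including all randomly assigned participants for whom data on the primary endpoint is available". The model is a linear regression "considering the outcome measures at the end of the training as a dependent variable and intervention/control as an explanatory variable", adjusted for baseline CWRET and taking centre into account. The only other set named is in the next sentence: "Secondary analysis will be conducted per-protocol (all completers".

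Under Outcome measures, CWRET is measured at baseline (T0) and once more, at T1. A patient without a T1 test therefore has no post-baseline value of the primary outcome.

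The Sample size section describes expected drop-out as high, gives no rate, and names the causes: "patients transferred to acute care, severely ill with fever, severe dyspnoea, acute respiratory failure". To cover this, "we will enrol at least 170 patients".

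The Analysis plan also examines completion against drop-out, through odds ratios for each baseline variable. That work is exploratory and does not feed into the treatment estimate.

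**The concern.** Having a T1 value is decided after randomisation. Several of the named reasons for loss arise during training and bear on exercise tolerance, the quantity that the primary endpoint measures. Loss could also differ by arm. The Background hypothesises that HFNT reduces dyspnoea, and severe dyspnoea is one of the named reasons. The intervention section foresees intolerance of flow and temperature, and the Randomisation section says that patients know their allocation.

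If so, the primary estimate describes patients well enough to be tested at T1, which need not equal the effect of assigning HFNT to everyone randomised. Baseline CWRET and centre can correct only for loss that they and the arm explain. Enrolling more patients protects precision and does nothing about bias.

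**Working it through.** **Inputs from the protocol article.** Sample size: difference 130 s, SD 250 s, 90% power, 5% significance, 156 participants, at least 170 enrolled. Randomisation: 1:1.

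**Inputs assumed.** The article gives neither loss by arm nor outcomes for drop-outs. Both are set as ranges below.

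**1. The plan's own figure.** n per arm = 2 × (1.960 + 1.282)² × (250/130)² = 77.7, rounded up to 78, so 156 in total. This reproduces the stated number with a two-sided test; a one-sided test would give 128. Power at 78 per arm is 90.1%.

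**2. Loss allowed for.** (170 − 156)/170 = 14/170 = 8.2%. With 170 enrolled, power is 89.5% at 10% loss, 87.8% at 15%, 85.8% at 20% and 81.0% at 30%. Power is not the main issue.

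**3. Bias of the available-data difference.** Let d be the share lost in an arm. Let g be the number of seconds by which the drop-outs' T1 outcome falls below that of tested patients in the same arm, after allowing for baseline and centre. The mean over all randomised patients in an arm is the tested mean minus d × g, so

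bias = d(HFNT) × g(HFNT) − d(V-mask) × g(V-mask).

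With the same g in both arms, from 150 to 400 s:

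| Loss, V-mask / HFNT | Bias |
|---|---|
| equal | 0 s |
| 5% / 11.5% | 0.065 × 150 to 0.065 × 400 = +10 to +26 s |
| 10% / 20% | 0.10 × 150 to 0.10 × 400 = +15 to +40 s |
| 20% / 10% | −15 to −40 s |

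With equal loss but g differing between arms by 100 to 200 s, the bias is 0.082 × 100 to 0.082 × 200 = 8 to 16 s at 8.2% loss, and 20 to 40 s at 20% loss. Its sign depends on which arm has the larger g.

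A wider gap goes beyond this range: 5% / 20% gives 0.15 × 150 to 0.15 × 400 = 22.5 to 60 s.

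**4. What that means for the test.** The standard error at 78 per arm is 250 × √(2/78) = 40.0 s. With no true effect and bias b, the two-sided error rate is Φ(−1.96 + b/40.0) + Φ(−1.96 − b/40.0). It is 6.6% for b = 15 s, 9.6% for 25 s and 17.0% for 40 s. As a share of the 130 s target, 15 to 40 s is 12% to 31%.

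**5. Whether the second set helps.** A patient lost before T1 is in neither set. A patient who stops training but is tested at T1 is in the modified intention-to-treat set and not among completers. The completer set is thus equal to the primary set or narrower. Agreement between the two analyses says nothing about patients without a T1 value.

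**The case against.** - **The article is condensed.** Imputation, missing-data scenarios and drop-out tables are commonly left to a SAP, and their absence here is not an error. This stands. What the article does fix is the primary set and the one alternative set, and a SAP would have to supplement that choice.
- **Available-data regression is not biased in itself.** If loss depends only on arm, baseline CWRET and centre, the planned model is valid. This stands. The doubt is whether that condition fits the listed causes, which arise after baseline.
- **The two sets need not coincide.** A reader might infer that they contain almost the same patients. No section restricts T1 testing to completers, so that inference is unsupported. The narrower point, that completers cannot test the missing-data assumption, remains.
- **Loss that differs by arm is a conjecture.** Fever has no obvious link to a device worn for 30-minute sessions, and the protocol provides for lowering flow and temperature when they are not tolerated. This is fair; no rate by arm can be drawn from the documents.
- **Drop-out by arm may be reported anyway.** The Analysis plan describes binary and categorical outcomes by group. This makes that part of the remedy the least essential.

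A reader might also infer that the planned analysis will overstate HFNT by about a third. One can construct such a figure. Take gains of 150 s and 280 s among tested patients, no gain in drop-outs, and losses of 15% on HFNT and 5% on V-mask. The all-randomised difference is then 0.85 × 280 − 0.95 × 150 = 95.5 s, and 130/95.5 is 36% too large. The documents do not support this as an estimate. The Sample size section gives 150 s as a minimal important difference and does not clearly make it the expected control mean; 280 s is merely 150 + 130. The 3:1 loss ratio is assumed, and setting drop-outs' gain to zero drives the result. At equal loss of 8.2% the same formula gives 0.918 × 130 = 119 s, a gap of 11 s against a standard error of 40 s. With losses reversed it gives 0.95 × 280 − 0.85 × 150 = 138.5 s, so the sign changes.

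**Conclusion.** The concern holds as a possibility that the plan leaves unchecked; bias is not shown to occur. The stated primary set excludes everyone without a T1 CWRET, the plan itself expects high loss from causes tied to exercise tolerance, and neither stated set can show whether this matters.

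The range of about 0 to 40 s in either direction rests on three assumptions: the deficit in drop-outs, loss rates of 5% to 20%, and a gap between arms of at most 10 percentage points, with unequal loss and unequal deficits taken one at a time. If loss stays near the 8.2% that the enrolment target covers, the bias is likely to sit in the lower part of that range; the text, however, calls drop-out high and sets 170 as a minimum. The 36% figure is an illustration only. Severity: should-fix.

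**What to change.** 1. State that T1 CWRET is sought in every randomised patient who is still in hospital at the planned T1 date and able to be tested, whether or not training was completed, and that patients are analysed by allocated arm.
2. Keep the regression adjusted for baseline and centre as the primary analysis. Prespecify a sensitivity analysis on all randomised patients by multiple imputation, using arm, centre, baseline CWRET, 6MWT, sessions completed and reason for stopping. The last two matter most: imputing from the primary model's own covariates would add almost nothing. Add a scenario with T1 = T0 for patients lost to deterioration.
3. Report drop-out and its reasons by arm.

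The cost is a few extra T1 tests in inpatients who stopped training, protocol or SAP wording, and modest programming. Some patients will be too ill to test, so some missing values will remain. Imputed values and the T1 = T0 scenario rest on assumptions that the data cannot verify, and should be presented as such. The T1 testing rule is the urgent part, because a test not done at T1 cannot be recovered later.

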### Outcome measures

At baseline (T0), anthropometric parameters, e.g. age, sex, body mass index, diagnosis, spirometry (FEV1, FVC, FEV1/FVC) [24] and comorbidities (using Cumulative Illness Rating Scale [25]), will be recorded. All other outcome measures described below will be assessed at T0 and at the end of the study period (T1, primary assessment time).

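### As most directly read, the analysis plan tests every secondary outcome in completers only; it should use all randomised patients with that outcome measured at T1

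*Protocol article*

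**What the plan says.** The Analysis plan of the protocol article names two analysis sets.

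- The primary analysis uses a modified intention-to-treat set, "including all randomly assigned participants for whom data on the primary endpoint is available". The only model carrying that label is for CWRET: "Primary analysis of the primary outcome will be through a linear regression model".
- The next sentence on sets reads "Secondary analysis will be conducted per-protocol (all completers").

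Three paragraphs later the same section gives the content of the secondary analysis: "Secondary analysis will consist of a two-sample *t* test comparing differences in the changes in all outcome measures after rehabilitation". No other between-arm test is given for the secondary outcomes.

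The section also promises a description without a test and without a named set: "The baseline, follow-up values and the unadjusted change in outcome measures between baseline and the end of study for both groups will be also presented". Under Outcome measures, the timing is the same for all of them: "All other outcome measures described below will be assessed at T0 and at the end of the study period (T1, primary assessment time").

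On losses, the Sample size section says: "Due to a high expected drop-out rate (patients transferred to acute care, severely ill with fever, severe dyspnoea, acute respiratory failure, etc".), at least 170 patients will be enrolled. No drop-out rate is stated.

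**The concern.** The per-protocol sentence and the t-test sentence carry the same label. Taken together, they restrict every test of the 6MWT, respiratory and limb muscle strength, MRC dyspnoea, blood gases, the two Barthel indices, CAT and MRF-26 to patients who completed.

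Completion is a post-randomisation event, and the protocol's own reasons for drop-out are what several of these outcomes measure. Patients know their allocation, and the Discussion expects HFNT to be better tolerated than NIV, so completion could plausibly differ by arm. If it does, the arm that loses more of its sicker patients looks better on these outcomes. Measurements taken at T1 in non-completers would also go unused.

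**Working it through.** **1. Which set applies to the secondary outcomes?**

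| Reading of the per-protocol sentence | Set for the secondary-outcome tests |
|---|---|
| It governs everything labelled secondary analysis (most direct) | Completers |
| It concerns CWRET only, as a companion to the modified intention-to-treat analysis | Not stated; the only other named set requires CWRET data |

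The second reading does not settle the matter. Having a cycling test result is not the right condition for entering a quality-of-life or blood-gas comparison. No sentence defines a set by whether the secondary outcome itself was measured.

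**2. The plan's own figures.** With a difference of 130 s, SD 250 s, 90% power and two-sided 5%:

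n per arm = 2 × (1.960 + 1.282)² × 250² / 130² = 77.7, rounded up to 78, so 156 in total. This reproduces the stated number.

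Enrolling 170 to retain 156 implies a loss of 1 − 156/170 = 8.2%, or 14 patients.

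**3. Size of a completers-only bias.** Let d₁ and d₂ be the non-completion proportions, and g the gap in mean change (in SD) between completers and non-completers, taken as equal in both arms. In each arm the completer mean exceeds the mean of all randomised patients by d × g. Hence:

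- bias = (d₂ − d₁) × g
- SE = √(1/[85(1 − d₁)] + 1/[85(1 − d₂)]), with 170 patients split 1:1 into 85 per arm
- type I error = P(|Z + bias/SE| > 1.96)

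The document gives neither d nor g. The values below are assumptions.

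| d₁ vs d₂ | g (SD) | Bias (SD) | SE | Bias/SE | Type I error |
|---|---|---|---|---|---|
| 5% vs 15% | 0.5 | 0.05 | 0.162 | 0.31 | 6.1% |
| 5% vs 15% | 1.0 | 0.10 | 0.162 | 0.62 | 9.5% |
| 4/85 vs 10/85 (14 of 170, the implied 8.2%) | 0.5 | 0.035 | 0.160 | 0.22 | 5.6% |
| 6.2% vs 10.2% (mean 8.2%) | 0.5 | 0.02 | 0.160 | 0.13 | 5.2% |
| equal | any | 0 | – | 0 | 5.0% |

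For the first row: 1/80.75 + 1/72.25 = 0.0262, whose square root is 0.162.

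A different model, in which drop-out and outcome are correlated at 0.3 to 0.7, gives biases of similar order: 0.04 to 0.08 SD for 5% versus 12%, and 0.05 to 0.11 SD for 10% versus 20%.

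**4. What the fix can recover.** These figures measure bias against all randomised patients. Analysing everyone with the outcome at T1 brings back only the non-completers who were assessed. The figures are therefore an upper bound on the gain, provided that loss without any T1 data does not run in the opposite direction between arms.

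**The case against.** The strongest reply is that the per-protocol sentence directly follows a set defined by the primary endpoint. There it may simply be the usual companion analysis of CWRET. The t-test sentence comes later, describes a method and names no set. This is a fair reading of a condensed article, and it means the restriction to completers is the most direct reading, not the only one. It still leaves no suitable set stated for the secondary outcomes.

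A reader might also infer more than the text supports:

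- **That patients are not analysed as randomised.** Nothing reassigns anyone. The test is described as "comparing differences in the changes in all outcome measures after rehabilitation between the intervention and control groups". The issue is who is left out, not which arm they are counted in. The descriptive tables and the recording of adverse events carry no completer restriction.
- **That a patient too breathless to cycle at T1 is excluded under either reading.** The Analysis plan speaks of completing or dropping out of the programme. A patient who finishes training but lacks a T1 CWRET may therefore count as a completer. Under Primary outcome, a Borg score of 8 ends the test and the time is recorded, so breathlessness by itself gives a short time, not a missing one.
- **That 6.1% or 9.5% is the cost of the plan's choice.** The 15% versus 5% split averages 10%, above the implied 8.2%. About 13 versus 4 of 85 would itself be a nominally significant imbalance (Fisher p = 0.038). Many of the listed drop-outs, such as transfers to acute care, may have no T1 data and would stay missing after the fix. If completer means assessed at T1, the fix recovers nobody; the article does not define the term.

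These points limit the size and certainty of the concern. They do not remove it.

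**Conclusion.** The point holds in a limited form. The Analysis plan, as most directly read, restricts every between-arm test of a secondary outcome to a set selected after randomisation, in a trial that expects losses from clinical worsening. On the alternative reading, the only other named set depends on CWRET data. This is a stated rule, not detail left to a statistical analysis plan.

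The size is unknown. Under the assumed 15% versus 5% non-completion and a 0.5 to 1 SD gap, the bias is 0.05 to 0.10 SD, with type I error of about 6% to 9.5%. At the implied 8.2% loss and a 0.5 SD gap it is smaller, about 5.2% to 5.6% in the splits shown. It is zero if completion is equal across arms and the gap is the same in both. The direction cannot be predicted. The primary analysis of CWRET is unaffected, so the change is advisable but does not bear on the main conclusion.

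**What to change.** In the Analysis plan, state that each secondary outcome is compared by allocated arm in all randomised patients who have that outcome measured at T1, whether or not they completed the sessions or have a T1 CWRET. Keep the completer analysis as a labelled sensitivity analysis, and say what counts as a completer.

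The cost is a sentence or two of text, with no new patients, visits or measurements. Patients without any T1 data remain missing, so the change reduces the selection and does not abolish it.

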#### Secondary outcomes

Functional capacity by the 6MWT carried out according to American Thoracic Society/European Respiratory Society recommendations [27].Respiratory muscle strength will be evaluated by maximal inspiratory pressure and maximal expiratory pressure. An electronic manometer (Precision Medical, Northampton, USA) will be used according to international recommendations [28].Peripheral muscle strength (biceps and quadriceps) will be evaluated by manual dynamometer (Chatillon^®^ X-3328Series, Ametek Inc., Florida, USA). The measure will be conducted using a hand-held dynamometer according to the position tests described by Andrews et al. [29]. For biceps, we will position patients sit on a chair, with adducted arm and elbow at 90° of flexion. We will ask patients to perform an elbow flexion and the dynamometer will be fixed at wrist level. For quadriceps, we will position patients sit on a high chair and ask them to perform a knee extension placing the dynamometer just over the ankle.Dyspnoea evaluation by the Medical Research Council scale [30].Respiratory exchanges by blood gas analysis. We will record the partial pressures of O_2_, CO_2_, O_2_/FiO_2_, and pH.Disability, measured by the Barthel Index [31] and Barthel Dyspnea Index [32].Impact of disease measured by the COPD Assessment test [33].Quality of life by the Maugeri Respiratory Failure Scale-26 [34], specifically dedicated to CRF patients.

Global patient satisfaction with the training sessions and oxygen device will be rated on a 5-point Likert scale [35] using a bespoke questionnaire. We will measure the satisfaction score the day after the training programme conclusion. We will ask patients the following questions: “How would you rate your feeling of comfort and well-being during training?” (0 = I think that it was not sufficient; 1 = sufficient; 2 = good; 3 = a bit heavy, 4 = too heavy for my physical condition); “What do you think about the oxygen delivery device used?” (0 = not sufficient (several problems), 1 = sufficient, 2 = good, 3 = very good, 4 = excellent). Adverse events that occur during exercise sessions and during hospital admission course will be registered. The outcome measures and the time-point of evaluations were described with the SPIRIT checklist (Fig. 3).

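### Secondary outcomes get an unadjusted t test on change scores, although the baseline- and centre-adjusted primary model could be used at no cost and would usually be more precise

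*Protocol article*

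**What the plan says.** The Analysis plan section confines the adjusted model to one outcome: "Primary analysis of the primary outcome will be through a linear regression model", "with adjustment for the baseline value of the primary outcome". It adds: "The model will also take into account the centre as a stratification variable". For the remaining outcomes, the only between-group test named is a two-sample t test "comparing differences in the changes in all outcome measures after rehabilitation between the intervention and control groups". No covariate or centre term is attached to it. The same section separately plans a descriptive presentation of baseline values, follow-up values and unadjusted changes by arm.

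The Randomisation section makes centre a design factor: "The participants will be randomised in variable blocks by centres", with "randomisation ratio 1:1". The Outcome measures section says "All other outcome measures described below will be assessed at T0 and at the end of the study period (T1, primary assessment time", so baseline values of the paired outcomes will be available. Satisfaction is the exception. It appears in the Secondary outcomes section, which says of it: "We will measure the satisfaction score the day after the training programme conclusion". The Abstract also places it at the end of training only.

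**The concern.** The plan uses baseline and centre where it has one outcome to analyse, and drops both for walking distance, respiratory and peripheral muscle strength, blood gases, disability, disease impact and quality of life. The covariates are collected anyway. A change score subtracts the whole baseline value, which amounts to fixing the slope on baseline at 1. The regression estimates that slope. When the true slope is below 1, the change score adds noise and over-corrects for any chance imbalance between arms at T0. What is at stake is the width of the secondary confidence intervals and the chance of detecting a real secondary effect. The primary result, the sample size and the type I error rate of the primary test are not touched.

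This is not a detail left to an analysis plan that is not shown: the article names the test and says which outcomes it covers.

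**Working it through.** **1. The plan's own figure.** Inputs from the Sample size section: difference 130 s, SD 250 s, 5% significance (taken as two-sided), 90% power. Per arm n = 2 × (1.960 + 1.282)² × 250² / 130² = 2 × 10.51 × 3.698 = 77.7, rounded up to 78, so 156 in total. The stated figure reproduces. It concerns the exercise test time only; no secondary outcome is powered in the document.

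**2. Change score against regression.** Let r be the correlation between the T0 and T1 values, and take equal SDs (σ) at both times. The within-arm variance is

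- change score: 2σ²(1 − r)
- baseline-adjusted regression: σ²(1 − r²)
- ratio of regression to change score: (1 − r²) / [2(1 − r)] = (1 + r)/2

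The document gives no r, so the range below is assumed. CI narrowing is 1 − √[(1 + r)/2]. Equivalent N is 156 × (1 + r)/2, the number with which the regression matches a change-score test on 156. The power column starts from a hypothetical outcome with 80% power under the t test: Φ(2.80/√[(1 + r)/2] − 1.96).

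| Assumed r | Variance ratio | CI narrower by | Equivalent N | 80% power becomes |
|---|---|---|---|---|
| 0.3 | 0.65 | 19% | 101 | 94% |
| 0.5 | 0.75 | 13% | 117 | 90% |
| 0.7 | 0.85 | 8% | 133 | 86% |
| 0.8 | 0.90 | 5% | 140 | 84% |
| 0.9 | 0.95 | 2.5% | 148 | 82% |

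A simulation with 156 patients (4,000 replicates) gave ratios of 0.76, 0.86 and 0.95 at r = 0.5, 0.7 and 0.9, against 0.75, 0.85 and 0.95 by formula.

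**3. Unequal SDs.** With k = SD at T1 / SD at T0, the slope on baseline is rk and the ratio is k²(1 − r²) / (k² + 1 − 2rk). At k = 1.25 and r = 0.8 the slope is 1 and the ratio is 0.5625/0.5625 = 1.00, so baseline adjustment gains nothing. At k = 0.8 and r = 0.5 it is 0.48/0.84 = 0.57, a larger gain than with equal SDs. In large samples the ratio never exceeds 1.

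**4. Centre.** Suppose centre explains a share c of the variance of the change score (assumed 2% to 10%; the document gives no figure). With allocation balanced within centres, the t test overstates the standard error by the factor 1/√(1 − c), which is 1.0% at c = 0.02 and 5.4% at c = 0.10. The true two-sided error rate is 2[1 − Φ(1.96/√(1 − c))], which is 0.048 and 0.039 instead of 0.05.

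**5. Satisfaction.** It is measured once, after training. No T0 value means no change, so a test of changes in all outcome measures cannot literally include it.

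**The case against.** The strongest reply is that this is a matter of efficiency, not error. Under randomisation the t test on changes is valid and unbiased for the same mean difference between arms that the regression targets. A reader might infer that the secondary estimates are biased, or cannot be set beside the primary result; neither follows. Regression to the mean from a chance imbalance is a feature of one sample, not a bias of the method.

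A reader might also infer a large loss on every outcome. The documents do not support that, because they give no correlations and no SDs for secondary outcomes. For measures repeated about a month apart, r of 0.8 to 0.9 is quite possible, and the gain is then only about 5% to 2.5% in CI width. Change scores also cancel stable differences in level between centres, so only centre differences in change remain, and ignoring them makes the test conservative rather than liberal.

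The t test might be read as a supportive analysis of everything, including the primary outcome, since the section also uses the term secondary analysis for the per-protocol set. That reading is possible, but the secondary outcomes would then have no other between-group test named, so the point stands.

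On satisfaction, the timing is plain from the Abstract and the Secondary outcomes section, and few analysts would be misled. It is a slip of scope, not a defect of design. Objecting to a t test on the short ordinal dyspnoea (Medical Research Council) scale would be largely a matter of preference, and is not pressed here.

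**Conclusion.** The point holds as an inexpensive improvement in precision. The named test is valid, but generally less precise than the model the plan already uses for its primary outcome, and it leaves chance baseline imbalance uncorrected. With equal SDs and r assumed between 0.3 and 0.9, confidence intervals would be about 19% to 2.5% narrower. A hypothetical power of 80% would rise to between about 94% and 82%. The gain is uneven across outcomes, and the baseline part disappears where the slope on baseline is near 1. Omitting centre adds slight conservatism: a standard error about 1% to 5% too large if centre explains 2% to 10% of the variance, which is also an assumption. The satisfaction issue is a minor wording correction.

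**What to change.** In the Analysis plan section, replace the t test for each continuous outcome measured at T0 and T1 with the primary model: the T1 value regressed on arm, that outcome's own T0 value and centre. Report the adjusted difference with its 95% CI. Keep the unadjusted changes as the descriptive presentation already planned. As a minor wording correction, exclude satisfaction from the change-score test, state that it is compared between arms at T1 only, and except it from the statement in the Outcome measures section that the outcomes are assessed at both times.

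The cost is about a paragraph of wording. No patients, visits or measurements are added. Baseline and seven centres use 1 + 6 = 7 of the 154 residual degrees of freedom available with 156 patients, which is immaterial.
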